## Abstract

**Background and Rationale:** Among the key players in the pathogenesis of Amyotrophic Lateral Sclerosis (ALS), microglia and T regulatory lymphocytes (Treg) are candidate cells for modifying the course of the disease. The gut microbiota (GM) acts by shaping immune tolerance and regulating the Treg number and suppressive function, besides circulating neuropeptides, and other immune cells that play in concert through the gut-brain axis. Previous mouse models have shown an altered enteric flora in early stage ALS, pointing to a possible GM role in ALS pathogenesis. Fecal Microbial Transplantation (FMT) is a well-known therapeutic intervention used to re-establish the proper microenvironment and to modulate enteric and systemic immunity.

**Methods:** We are going to perform a multicenter randomized double-blind clinical trial employing FMT as a therapeutic intervention for ALS patients (NCT0376632). Forty-two ALS patients, at an early stage, will be enrolled with a 2:1 allocation ratio (28 FMT-treated patients vs. 14 controls). Study duration will be 12 months per patient. Three endoscopic procedures for intestinal biopsies in FMT and control groups are predicted at baseline, month 6 and month 12; at baseline and at month 6 fresh feces from healthy donors will be infused at patients in the intervention arm. The primary outcome is a significant change in Treg number between FMT-treated patients and control arm from baseline to month 6. Secondary outcomes include specific biological aims, involving in-depth analysis of immune cells and inflammatory status changes, central and peripheral biomarkers of ALS, besides comprehensive analysis of the gut, saliva and fecal microbiota. Other secondary aims include validated clinical outcomes of ALS (survival, forced vital capacity, and modifications in ALSFRS-R), besides safety and quality of life.

**Expected Results:** We await FMT to increase Treg number and suppressive functionality, switching the immune system surrounding motorneurons to an anti-inflammatory, neuroprotective status. Extensive analysis on immune cell populations, cytokines levels, and microbiota (gut, fecal and saliva) will shed light on early processes possibly leading the degenerative ALS course.

**Conclusions:** This is the first trial with FMT as a potential intervention to modify immunological response to ALS and disease progression at an early stage.

## Introduction

When questioning why so many failures in clinical trials in amyotrophic lateral sclerosis (ALS), the lack of a complete comprehension of the pathogenic systems behind the disease onset and progression might be accounted as one of the main reasons. Indeed, ALS is a complex syndrome. Aberrant cellular pathways convey from protein misfolding, with endoplasmic reticulum stress, defective autophagy and damage to cytoskeleton (1), associated to staggered RNA processing and mitochondria homeostasis, increased oxidative stress, enhanced excitotoxicity, reduced neurotrophic sustenance, and to a glial inflammatory response that is oriented toward a harmful side (2).

Recent studies highlighted the role of microglia and opened new perspectives in the knowledge of the non-cell autonomous molecular mechanisms possibly contributing to ALS, launching them as a plausible target for many clinical trials. During ALS progression, activated microglia switch from the M2 phenotype, which is neuroprotective and supports tissue repair and neuron survival through the release of neuroprotective factors, to M1 phenotype, which is toxic and contributes to neuronal death through pro-inflammatory cytokines production, and tissue destruction. Therapeutic approaches targeting microglia polarization to induce the M2 phenotype are promising strategies to contain local neurodegeneration and improve ALS outcome (3). Indeed, in animal models of the disease, diminishing the mutant levels of microglia sharply slowed later disease progression (4).

M1/M2 macrophages phenotypes switch have been shown to be induced by CD4^+^ T cells, especially CD4^+^CD25^+^Foxp3^+^ T regulatory (Treg) cells (5, 6). In the blood and spinal cord of patients with ALS, CD4^+^ T cells (T helper—Th) are increased, especially with a predominantly pro-inflammatory Th1/Th17 phenotype (7). On the contrary, Tregs from blood of ALS patients demonstrated a significant decrease in the ability to suppress the proliferation of the effector T cells; and of note, the loss extent in suppression was correlated with disease progression (7). The passive transfer of mSOD1 Tregs into ALS mice lacking functional T lymphocytes prolonged their survival while FoxP3 mRNA in the spinal cord of mSOD1 mice inversely correlated with disease progression (8). Finally, in ALS patients the Tregs' number and percentage, and FoxP3 expression decreased with faster disease progression and were early predictors of ALS progression and survival (8, 9).

Very recently, autologous infusions of expanded Treg cells and concomitant IL-2 into patients with ALS resulted to be safe and tolerable during early and later stages of disease in a phase I study, where infusions seemed to slow progression rates (10). Moreover, the study detected a correlation between Treg suppressive function and disease progression, underscoring the rationale underlying the use of Treg suppressive functionality as an indicator of clinical status (10).

All these evidences convey toward a dysfunction of the adaptive immune response during ALS. Increasing data suggest that the systemic immune response and especially the neuroimmune system can be modulated by gut microbiota (GM) through the gut-brain axis, a key player in the regulation of mutual signaling between gut microflora and central nervous system (CNS) (11, 12) employing bidirectional communication via neuronal, hormonal, immunologic, and toxic signaling (13–15).

Intestinal microbiota includes a complex ecosystem with an exceptionally high bacterial density and diversity: the adult alimentary tract contains 1–2 kg of microbial cells of hundred bacterial species, of which over 80% have not been cultured (16–18).

GM communicates straightforward with the enteric immune system, shaping immune tolerance and thus contributing to the modulation of immune reactions during inflammation (19). Conversely, upon pathogen invasion, dysbiosis or barrier break, the microbe-associated molecular patterns stimulate macrophages and dendritic cells to produce pro-inflammatory cytokines. In turn, the cytokine activate the adaptive immune cells, thus contributing to the breakdown of immune homeostasis (20), and typically, determines loss of the immune cells that keep the aggressiveness of the immune system in check, namely Tregs (12).

Several brain biological processes may be influenced by GM alterations. Germ free mice have been found to have an altered density, morphology and maturity of microglia, and treatment with a short chain fatty acids (SCFA) mixture restored the density and morphology of CNS immune cells, suggesting that GM can influence both the development and functions of microglia (12, 21).

In ALS, GM dysbiosis may facilitate the disease onset or drive its progression and related outcomes, in the presence of other risk factors. Alternately, the GM dysbiosis may be (further) altered by the disease presence and in some individuals contribute to disease progression, prognosis, also in terms of variable response to drug treatments (22).

An alteration in the intestinal bacterial flora as an external trigger could explain the rare cases of ALS in spouses or in some clusters (23).

Based on these premises, to treat GM dysbiosis through microbiota restoration would have the potential to interfere and slow ALS progression (24).

Our trial aims at evaluating the biological basis of a potential treatment for ALS (namely fecal microbiota transplantation, FMT) in order to plan a following efficacy study.

The primary objective is to evaluate if FMT augments Tregs' number in ALS patients, treated with FMT compared to the control arm and measured at baseline and at month 6.

The secondary objectives include specific biological aims: (i) comparison between treated patients and control arm of Tregs'number and T cell subsets at different time points in blood and gut tissue samples; (ii) comparison between treated patients and control arm of neurophylaments and CSF cytokines and cells; (iii) analysis of fecal and saliva samples between the two groups to evaluate microbiota and cytokines' profile; (iv) FMT safety and tolerability in ALS; (v) clinical assessment (including tracheostomy-free survival, Forced vital capacity score, ALSFRS-R score, frequency of PEG or NIV); finally, (vi) the Quality of Life (QoL) assessment.

## Methods and Analysis

### Study Design

We are going to perform a randomized double blind multi-center study on FMT in ALS.

The Figure 1 summarizes the study design.

**Figure 1 F1:**
[figure not shown]
Picture of the study design.

The study will include 42 ALS patients with 2:1 allocation in 2 groups of subjects (28 FMT vs. 14 controls). Patients will be screened in the 15 days before baseline; then they will be randomly allocated to either FMT or control group. Randomization will be 2:1 (FMT: controls) and will be performed on line (using a computer-generated list of random number that will be centrally generated in the Statistical Unit). Given the heterogeneous ALS progression, patients will be stratified by ΔFS (progression rate), calculated at randomization according to Kimura et al. (25). Riluzole will be maintained during the entire study duration unless adverse events or patients' decision to withdraw. Endoscopic treatment will be performed within 21 days from randomization. Randomization number will not be re-used in any case. Estimated enrolment time is 18 months.

### Study Population

The study will include probable laboratory-supported, clinically probable, or definite ALS according to revised El Escorial criteria (sporadic and familiar). Inclusion and exclusion criteria for the enrolment of the patients are presented in the Table 1.

**Table 1 T1:** Inclusion and exclusion criteria for patients.

**Inclusion criteria**	**Exclusion criteria**
– Patients diagnosed with a laboratory supported, clinically “probable” or “definite” amyotrophic lateral sclerosis according to the Revised El Escorial criteria – Sporadic or familial ALS – Female or male patients aged between 18 and 70 years old – Disease duration from symptoms onset no longer than 18 months at the screening visit – Patients treated with a stable dose of Riluzole (100 mg/days) for at least 30 days prior to screening – Patients with a weight >50 kg and a BMI ≥18 – Patients with a FVC equal or more than 70% predicted normal value for gender, height, and age at the screening visit – Patients able and willing to comply with study procedures as per protocol – Patients able to understand, and capable of providing informed consent at screening visit prior to any protocol-specific procedures – Use of effective contraception both for males and females	– Known organic gastrointestinal disease – History of gastrointestinal malignancy; ongoing malignancies – Use of immunosuppressive or chemotherapy within the past 2 years – Celiac disease and/or food (e.g., lactose) intolerance – Previous gastrointestinal surgery – Any condition that would make endoscopic procedures contraindicated – Acute infections requiring antibiotics – Antimicrobial treatment or probiotics 4 weeks prior to screening – Severe comorbidities (heart, renal, liver failure); severe renal (eGFR < 30 ml/min/1.73 m^2^), or liver failure or liver aminotransferase (ALT/AST > 2x Upper limit of normal), – Autoimmune diseases, inflammatory disorders (SLE, Rheumatoid arthritis, connective tissue disorder) or chronic infections (HIV, hepatitis B, or C infection, Tuberculosis) – Abuse of alcohol or drugs – Participation in clinical trials <30 days before screening – Existing blood dyscrasia (e.g., myelodysplasia) – White blood cells <4,000/mm3, platelets count <100,000/mm3, hematocrit <30% – Patients who underwent non-invasive ventilation, tracheotomy and /or gastrostomy – Women who are pregnant or breastfeeding

*BMI, Body Mass Index; FVC, Forced Vital Capacity; eGFR, estimated Glomerular Filtration Rate; ALT, alanine aminotransferase; AST, aspartate aminotransferase; SLE, Systemic Lupus Erythematosus*.

### Interventional Methods

Treatment will be double blinded to patients and neurologists, but not to the endoscopist and microbiologist. ALS patients will undergo upper GI endoscopy with small-intestine biopsies (*n*° 4 biopsies of small intestine, performed with a standard biopsy forces) at baseline and after 6 and 12 months. At baseline, the patients will be randomized (2:1) to either an allogenic (from donors) infusion of collected feces (60 grams) (FMT) in the duodenum-jejunum or no treatment (control group). The infusion will be performed through a standard nasojejunal tube that will be placed during endoscopy. Fecal infusion will be repeated at month 6. Control group patients will not receive any treatment (at baseline or at month 6), but will remain blind to treatment because of sedation due to small-intestine biopsies. Fecal microbiome will be diluted in saline solution (200 ml) and infused at 30 ml/min speed (whole amount of the performance: 15 min). Fresh feces for the FMT will be obtained by habitual healthy donors for *Clostridium difficile* infection. The Table 2 shows the blood and stool testing for donators and the general selection criteria. Before preparation, sample donation will be always analyzed by rapid molecular test to detect intestinal pathogens.

**Table 2 T2:** Criteria for donors' selection.

**EXCLUSION CRITERIA**		
**Infectious diseases risk**	**Gastrointestinal, metabolic and neurological disorders**	**Drugs that can impair gut microbiota composition**
▸ History of, or known exposure to, HIV, HBV, HCV, syphilis, HTLV1-2, tuberculosis, malaria, trypanosomiasis ▸ Known systemic infection not controlled at the time of donation ▸ Use of illegal drugs ▸ Risky sexual behavior ▸ Previous reception of tissue/organ transplant ▸ Recent (<12 months) reception of blood products ▸ Recent (<6 months) needle stick accident ▸ Recent (<6 months) body tattoo, piercing, earring, acupuncture ▸ Recent medical treatment in poorly hygienic conditions ▸ Risk of transmission of prions diseases ▸ Recent parasitosis or infection from rotavirus, *Giardia lamblia*, and other microbes with GI involvement ▸ Recent (<6 months) travel in tropical countries, countries at high risk of communicable diseases or traveller's diarrhea ▸ Recent (<6 months) history of vaccination with a live attenuated virus, if there is a possible risk of transmission ▸ Healthcare workers (to exclude the risk of transmission of multidrug-resistant organisms) ▸ Individual working with animals (to exclude the risk of transmission of zoonotic infections)	▸ History of inflammatory bowel syndrome or disease, functional chronic constipation, coeliac disease, other chronic GI disorders ▸ History of chronic, systemic autoimmune diseases with GI involvement ▸ History of, or high risk for, GI cancer or polyposis ▸ Recent appearance of diarrhea, hematochezia ▸ History of neurological/neurodegenerative diseases ▸ History of psychiatric conditions determining mental health instability or incapacity ▸ Overweight and obesity (body mass index >25)	▸ Recent (<3 months) exposure to antibiotics, immunosuppressants, chemotherapy ▸ Chronic therapy with proton pump inhibitors
**ISSUES TO ADDRESS ON THE SAME DAY OF DONATION TO CHECK ANY RECENTLY ONSET OF HARMFUL EVENTS**		
The following issues, if present, contraindicate donation on the same day on which they are assessed: ▸ Newly appeared GI signs and symptoms, for example, diarrhea, nausea, vomiting, abdominal pain, jaundice ▸ Newly appeared illness or general signs as fever, throat pain, swollen lymph nodes ▸ Use of antibiotics or other drugs that may impair gut microbiota, new sexual partners, or travels abroad since the last screening ▸ Recent ingestion of a substance that may result harmful for the recipients ▸ Travel in tropical areas—contact with human blood (sting, wound, showing, piercings, tattoos)—sexual high-risk behavior ▸ Diarrhea (more than three loose or liquid stools per day) among members of the entourage (including children) of the donor		
**BLOOD AND STOOL TESTING TO CHECK DONORS FOR ANY POTENTIALLY TRANSMITTABLE DISEASE**		
**General blood testing**	**General stool testing**	
▸ Cytomegalovirus ▸ Epstein-Barr virus ▸ Hepatitis A ▸ HBV ▸ HCV ▸ Hepatitis E virus ▸ Syphilis ▸ HIV-1 and HIV-2 ▸*Entamoeba histolytica* ▸ Complete blood cell count with differential ▸ C-reactive protein and erythrocyte sedimentation rate ▸ Albumin ▸ Creatinine and electrolytes ▸ Aminotransferases, bilirubin, gamma-glutamyltransferase, alkaline phosphatase	▸ Detection of *Clostridium difficile* ▸ Detection of enteric pathogens, including *Salmonella, Shigella* ▸*Campylobacter, Escherichia coli* O157 H7, *Yersinia*, vancomycin-resistant enterococci, methicillin-resistant *Staphylococcus aureus*, Gram-negative multidrug-resistant bacteria ▸ Norovirus ▸ Antigens and/or acid fast staining for *Giardia lamblia* and *Criptosporidium parvum* ▸ Protozoa (including *Blastocystis hominis*) and helminths ▸ Fecal occult blood testing	
**Blood testing in specific situations**	**Stool testing in specific situations**	
▸ Human T-lymphotropic virus types I and II antibodies *Strongyloides stercoralis*	▸ Detection of *Vibrio cholera* and *Listeria monocytogenes* ▸ Antigens and/or acid fast staining for *Isospora* and *Microsporidia* ▸ Calprotectin ▸*Helicobacter pylori* fecal antigen ▸ Rotavirus	

Analysis of T cell sub-populations will be performed both in peripheral blood and gut mucosa: Treg, Th17 cells, effector, and central memory cells.

At the end of the treatment period, further 6 months will be required as a follow-up period. This time is intended to assess late adverse events (AEs) and later biological or clinical effects of transplantation.

### Sample Size Estimation

Sample size was calculated considering as primary outcome measure the proportion of patients, in the transplantation group with respect to controls, displaying a “positive response” intended as an increase in the proportion of Treg by at least 20%. The null hypothesis states that FMT does not ameliorate significantly the proportion of positive responses in treated patients after the second FMT round, compared to their baseline and to control group. The alternative hypothesis is that FMT gives a proportion of positive responses in at least 50% of treated patients compared to a maximum 5% of positive responses in patients of the control group. The study was designed to refuse the null hypothesis with an alpha error of 0.05 and a power of 0.80 according to previously published statistical methods (26) and to known levels of Tregs in ALS patients, that typically display a slight reduction of Treg % (mean ± standard deviation: 2.1 ± 0.7) with respect to healthy controls with fast progressors patients having on average 31% fewer Treg (8, 27).

For this purpose, a population of 39 patients randomized in two treatment arms would suffice; taking into account an average drop out of 10%, a recruitment of 42 patients will be needed.

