As for clinical outcome measures, we will compare ALSFRS-R total score and subscores (bulbar, respiratory, gross, and fine motor) changes from baseline to each time point in treatment arm vs. control arm. Frequency of procedures (PEG, NIV, IV) will be compared from baseline to each time point in treatment vs. control arm. The comparison of clinical endpoint among arms will be carried out by using the logistic regression model. Results will be presented as odds ratios (OR) and 95%C.I. FMT will be considered effective in relation to controls whether the OR of positive results will provide a *p* < 0.05. Change in FVC during the study will be analyzed using a mixed model for repeated measures (MMRM). Difference between treatment groups and two-sided 95% CI will be estimated .Log-rank tests via Kaplan-Meier method will be employed to compare differences in tracheostomy-free survival between the two treatment arms (from onset and from randomization), while Cox's proportional hazard model will be used for adjusting for any possible unbalanced prognostic factors. Statistical significance will be set at 0.05 level for a two-tailed test. Last observation will be considered for patients with missing data.

Given the short duration of the study, an interim analysis of efficacy data is not scheduled. Nevertheless, to address safety concerns, a report including all relevant clinical data of patients will be sent by the Statistics Unit to an independent Data and Safety Monitoring Board for scheduled DSMB meetings (also through Skype) when 14 patients would have completed the second treatment and then every 6 months.

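### The stated drop-out allowance does not follow from its own inputs: 42 recruits with 10% loss leave about 38 patients, not 39 (minor; the 80% power claim stands)

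*Protocol article*

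**What the plan says.** The Sample Size Estimation section of the protocol article sets the size on a responder comparison, with response in "at least 50% of treated patients compared to a maximum 5% of positive responses in patients of the control group", and with "an alpha error of 0.05 and a power of 0.80". It concludes that "a population of 39 patients randomized in two treatment arms would suffice" and, in the same sentence, that "taking into account an average drop out of 10%, a recruitment of 42 patients will be needed".

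The Study Design section carries the 42 into the design: "The study will include 42 ALS patients with 2:1 allocation in 2 groups of subjects (28 FMT vs. 14 controls"). The Data Analysis section adds "Statistical significance will be set at 0.05 level for a two-tailed test" and, on missing data, "Last observation will be considered for patients with missing data".

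The article does not say how the 39 was inflated or how the result was rounded.

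**The concern.** The base size, the loss rate and the recruitment target are all printed, so the last should follow from the first two in one step. It does not. A drop-out allowance exists to secure a stated minimum after losses, which is why it is normally rounded up. Here the target falls short of that minimum at the stated loss rate.

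What is at stake is the accuracy of the sample-size statement. A reader would take 42 to protect 39 completers against 10% drop-out, when it protects them against about 7%.

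**Working it through.** **Inputs.** From Sample Size Estimation: 39 patients before drop-out, 10% drop-out, 42 recruited, response 50% (FMT) against 5% (control), alpha 0.05, power 0.80. From Study Design: 2:1 allocation, 28:14. From Data Analysis: two-sided testing.

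**1. Trying to reproduce 42.**
- Standard inflation, N/(1 − d): 39/0.90 = 43.3, rounded up to 44. The next exact 2:1 split is 45 (30:15).
- Common shortcut, N × (1 + d): 39 × 1.10 = 42.9, rounded up to 43.
- 42 appears only if the shortcut is used and 42.9 is then rounded down. 42 is also the multiple of 3 just below 42.9, which may be how it arose, but the article does not say so.

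**2. What 42 delivers.**
- Expected completers at 10% loss: 42 × 0.90 = 37.8, which is 39 − 37.8 = 1.2 below the stated 39.
- By arm: 28 × 0.90 = 25.2 and 14 × 0.90 = 12.6, so about 25:13.
- Largest drop-out that still leaves 39: (42 − 39)/42 = 3/42 = 7.1%.

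**3. Whether power is affected.** The article names no test for the comparison of responder proportions, so a two-sided Fisher exact test at 0.05 is assumed here. Power is the sum, over all pairs of responder counts with p ≤ 0.05, of the product of the two binomial probabilities at 50% and 5%.

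| FMT : control | Total | Power |
|---|---|---|
| 28:14 | 42 | 0.906 |
| 26:13 | 39 | 0.867 |
| 25:13 | 38 | 0.839 |
| 25:12 | 37 | 0.788 |
| 24:12 | 36 | 0.815 |

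The values do not rise smoothly with size because the test is discrete. Averaged over independent 10% drop-out in each arm, starting from 28:14, power is 0.823. A normal approximation gives 0.87 at 25:13 and 0.85 at 25:12.

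**4. Whether 39 itself is sound.** At 26:13 the assumed test gives 0.867, so 39 does suffice for 0.80. The uncorrected two-proportion formula at 2:1 gives 36, and exact power at 24:12 is 0.815. Thus 39 is enough, but it is not a threshold below which 80% is lost.

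**The case against.** The strongest reply is that nothing follows from the slip. The shortfall is 1.2 patients, and 42 is within one of the shortcut's 42.9 and within two of the correct 44. It gives an exact 2:1 split. It also equals six clinical centers each randomizing at least seven patients, the figures in Role of Participating Centers. These are plausible reasons for choosing 42, though the article gives none of them. As explanations of the choice they may be right; they do not make the printed step from 39 and 10% to 42 correct.

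Drop-outs may also not all leave the analysis. Data Analysis uses the last observation for missing data, and the study flow chart schedules a Treg measurement at month 3. The rule stands in the paragraph on clinical outcomes, so its reach to the primary comparison is uncertain. Even if every drop-out stayed in and counted as a non-responder (0.90 × 50% = 45% against 0.90 × 5% = 4.5%, at 28:14), power under the assumed test would be 0.84. This softens the practical effect. It does not rescue the sentence, which makes an allowance for drop-out.

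A reader might infer that the trial is underpowered, or that its margin over 80% is smaller than claimed. The document supports neither. It claims a power of 0.80 and no margin above that, and 0.80 is met at the expected number of completers. Single splits such as 25:12 fall just below (0.788) under Fisher's test, but the average over random drop-out does not. That part of the objection stands in full.

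**Conclusion.** Wrong as written, and minor. The step from 39 with 10% drop-out to 42 is an arithmetic or rounding slip of about one patient. The allowance covers 7.1% drop-out, not 10%.

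The planned power is kept at about 0.82 to 0.84. That rests on the plan's own rates of 50% and 5%, drop-out unrelated to response and counted as lost, and a two-sided Fisher test that is assumed here. The arithmetic on 39, 10% and 42 needs none of these assumptions. The slip gives no reason to recruit more patients or to change the analysis, and it belongs at the lowest severity.

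**What to change.** Keep 42 and the 10% assumption, and restate the last sentence of Sample Size Estimation. It should say that with 10% drop-out about 38 of the 42 patients (25:13) are expected to be evaluable; that this gives about 82–84% power for 50% against 5% under a two-sided Fisher exact test, or the corresponding figure for whichever test is intended, named in the text; and that 42 secures 39 completers only up to about 7% drop-out. Lowering the drop-out assumption to 7% to fit the chosen number is not advised, because that would tailor the assumption to the answer.

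The cost is one sentence, with no extra patients and no change to design or analysis.
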